#### Sampling strategy for baseline assessment.

In total, 1260 adolescents will be recruited from 12 schools (4 schools per city) across three cities in Northern India (Fig 3). These four schools per city will be divided into two government schools and two private schools for socio-economic representation. Each city will recruit 420 adolescents, 105 students per school. We will randomly select 4 classes from the pool of eligible 9^th^-, 10^th^-, 11^th^, and 12th-grade classes, assuming an average class size ranging between 25 and 35 students.

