### Participants

The study focuses on adolescents, specifically school students in the 9^th^, 10^th^, 11^th^, and 12^th^ grades (aged 14–17 years). The inclusion and exclusion criteria for the enrolment of study participants are described below:

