#### Sample size for baseline assessment.

For Phase 1 (baseline assessment), the sample size is calculated using the formula n = 4pq/d^2^ [9]. Where n is the sample size for each area of Tricity, p is the prevalence, q is 1-p, and d is precision. The proportion of adolescents in India is approximately 20% [10]. The prevalence of alcohol consumption among adolescents at least once a year ranged from 10.6% to 32.9% [11]. *Prevalence of sexual activity ranged between 16.9%* [12] *to 21%, and sizable numbers of Indian adolescents were facing parent-child conflicts. Therefore,* assuming a prevalence of 20%, a precision of 4%, and an attrition rate of 5%, the target sample size is calculated as 420 for each of the three cities. Taking an equivalent number of samples from each of the three cities, the final sample size for all three study areas is 1260.

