#### Sampling strategy for randomized controlled trial.

The same COHORT from the pre-intervention phase (baseline assessment) will be followed. Therefore, the 12 schools will be randomly selected into 6 intervention groups and 6 control groups, as shown in Fig 2.

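### The class draw is not stratified by grade: four classes come from one pool of grades 9 to 12, which leaves the grade mix of schools, cities and arms to avoidable chance

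*Protocol article*

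**What the plan says.** The Participants section sets the target population: "The study focuses on adolescents, specifically school students in the" 9th to 12th grades, aged 14 to 17.

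The section on the sampling strategy for the baseline assessment fixes the numbers: "1260 adolescents will be recruited from 12 schools (4 schools per city) across three cities in Northern India", and "Each city will recruit 420 adolescents, 105 students per school". On classes it says "We will randomly select 4 classes from the pool of eligible" 9th- to 12th-grade classes, "assuming an average class size ranging between 25 and 35 students". The only stratification stated is of schools: they are "divided into two government schools and two private schools for socio-economic representation" in each city. Nothing is said about grade. The section refers to Fig 3 for the sampling strategy; that figure is not shown.

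The section on the sampling strategy for the randomised trial carries the sample forward: "The same COHORT from the pre-intervention phase (baseline assessment) will be followed", with 6 schools allocated to each arm. The Statistical analysis section adjusts the GEE for socio-demographic and economic variables without listing them, and refers to S6 File (not shown) for the model.

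**The concern.** There are four grades and exactly four classes per school, so one class per grade would fit the planned numbers. As worded, the draw is from one pool. A school can then supply two or three classes of one grade and none of another.

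Alcohol use, sexual behaviour and social media use plausibly change between ages 14 and 17. If they do, the grade draw adds variation between schools, which are the randomised units, and only 6 per arm are available to average it out.

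Two things are at stake. The first is the baseline survey: each city's prevalence rests on four schools and would depend partly on which grades were drawn. The second is how alike the two arms look in age and grade.

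**Working it through.** **The plan's own figures.** From the baseline sample size section, p = 0.20, d = 0.04 and attrition is 5%.
- n = 4pq/d² = 4 × 0.20 × 0.80 / 0.04² = 400, and 400 × 1.05 = 420 per city.
- 420 / 4 = 105 per school, and 420 × 3 = 1260.
- 105 / 4 = 26.25 pupils per class, inside the stated class size of 25 to 35.

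The four-class design reproduces.

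**Assumption.** The documents do not give the number of sections per grade, s. I take s = 2, 3, 4 or 6, the same in every grade and school, with classes of equal size.

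**Chance that one school covers all four grades.** Four classes are drawn without replacement from 4s, so P = s⁴ / C(4s, 4).

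| s | P(all four grades) | P(a grade is missed) | Expected schools of 12 missing a grade |
|---|---|---|---|
| 2 | 16/70 = 0.229 | 0.771 | 9.3 |
| 3 | 81/495 = 0.164 | 0.836 | 10.0 |
| 4 | 256/1820 = 0.141 | 0.859 | 10.3 |
| 6 | 1296/10626 = 0.122 | 0.878 | 10.5 |

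With only five eligible classes (2, 1, 1, 1), P = 2/C(5, 4) = 0.40, so 60% of schools still miss a grade. With exactly one class per grade the probability of missing one is zero, but then there is nothing to draw.

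**Arm difference in mean grade.** Grades 9 to 12 in equal numbers have variance 1.25, so the finite-population variance is S² = 1.25 × 4s/(4s − 1). A school's mean grade has variance V = (S²/4) × (1 − 4/(4s)). With 6 schools per arm, SD = √(2V/6).
- s = 2: V = 0.179, SD = 0.24
- s = 3: V = 0.227, SD = 0.28
- s = 4: V = 0.250, SD = 0.29
- s = 6: V = 0.272, SD = 0.30

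A simulation of 40,000 draws of 12 schools gave the same SDs. In 34% to 44% of draws the share of classes in grades 11 and 12 differed between arms by at least 12.5 points (3 of 24 classes).

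**City baseline prevalence.** With four schools per city, the SD of the city mean grade is √(V/4): √(0.179/4) = 0.21 for s = 2 and √(0.272/4) = 0.26 for s = 6. To turn this into prevalence needs a gradient per grade, which the documents do not give. Two illustrations, each stretching a cited range across the three steps from grade 9 to 12:
- Steep: (32.9 − 10.6)/3 = 7.43 points per grade. The grade draw alone gives a 95% range of about ±3.1 to ±3.8 points, against a planned precision of 4.
- Shallow, using the cited range for sexual activity: (21 − 16.9)/3 = 1.37 points per grade. The range is about ±0.6 to ±0.7 points.

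**With one class per grade.** Every school has one class of each grade and each arm has 6 of each, so the class-level imbalance is zero. Pupil-level imbalance is then small but not exactly zero, because class sizes and consent rates differ.

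**The case against.** The case against has real weight.

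- **The intervention effect is largely protected.** Outcomes are measured in the same pupils at T0 and at T1 to T4, and the GEE addresses change with socio-demographic adjustment. A stable difference in level between grades is present at T0 as well, so most of it drops out. What remains is mainly any grade-by-time or grade-by-intervention effect, which cannot be sized from the documents. This stands.
- **The gradient is not in the documents.** The baseline sample size section says "The prevalence of alcohol consumption among adolescents at least once a year ranged from 10.6% to 32.9" per cent and does not tie that range to grade. A reader might take 7.43 points per grade as the protocol's own figure, or set the resulting noise in alcohol prevalence against the 5% effect in the trial sample size. Neither is supported: the range is not by grade, and that calculation pairs 5% with an SD of 0.15 and names no outcome.
- **The text may be shorthand.** Fig 3 is missing and an article condenses the full protocol, so a draw by grade may be specified elsewhere. This stands as a caveat. It does not change what the sentence says.
- **A simple draw is valid.** It gives every eligible class in a school the same chance of selection. One class per grade does not when sections per grade differ. This is a fair cost to set against the gain.
- **Recruitment has begun.** It started on 01/11/2025, so some classes may already be chosen.

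Two points survive. No adjustment is described for the baseline prevalences, and an avoidable source of variation between schools can be removed at almost no cost.

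**Conclusion.** The point holds as a cheap improvement in precision and comparability. As worded, the draw ignores grade. For any school with five or more eligible classes spread over the four grades, missing a grade is more likely than not in the configurations checked (60% to 88%). For 2 to 6 sections per grade, full coverage has probability 12% to 23%, and the arm difference in mean grade has an SD of 0.24 to 0.30 grade.

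A reader might infer that the comparison of arms is biased, or that most schools are certain to miss a grade. The documents support neither. The imbalance is random and favours no arm, and the coverage figures rest on an assumed number of sections. Nor does the protocol contradict itself, since it nowhere promises one class per grade.

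The effect on outcomes could be trivial or noticeable, depending on an unknown gradient. It matters more for the city baseline estimates than for the intervention effect.

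**What to change.** In the section on the sampling strategy for the baseline assessment, replace the class-selection sentence with, for example: *In each school, one class will be drawn at random from each of grades 9, 10, 11 and 12.* Apply it to schools not yet sampled, and name grade as a covariate in the outcome models. Where classes are already drawn, the covariate is the fallback. If Fig 3 or the full protocol already stratifies by grade, only the sentence needs aligning.

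The cost is small. The plan keeps four classes and 105 pupils per school, 1260 in total, with no extra visits. Where sections per grade differ, a class in grade g has selection probability 1/s for that grade, so the baseline prevalences may need simple weights proportional to the number of sections. Differences in class size and consent will leave a small residual imbalance, which the covariate can absorb.

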**Fig 3 pone.0354663.g003:**
[figure not shown]
Sampling strategy of the study.

#### Tools and materials used.

The assessment will be done by visiting the schools included in the sample and administering the standardized tools, including the Social Media Use Scale (SMUS) [13], Family Relationship Scales [8], Family Leisure Activity Profile [8], WHO’s Alcohol Use Disorders Identification Test (AUDIT) [14], and the Sexual Health Practice Tool. The questionnaire will undergo content validation in the North Indian context through expert review by professionals in public health, reproductive health, social sciences, and mental health. Pre-testing on 10% of the sample (≈120 adolescents) will ensure clarity, with language corrections as needed. Test-retest reliability will be measured using Cronbach’s Alpha. The details and early versions of the tools are attached in the S2 and S3 File.

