### Phase 3: Post-intervention phase

Assessments of outcomes will be conducted after completing the three-month intervention phase and for three months following the intervention closure. The Social Media Use Scale (SMUS), Family Relationship Scales, Family Leisure Activity Profile, WHO’s Alcohol Use Disorders Identification Test (AUDIT), and Sexual Health Practice Tool tools will be administered at baseline (T0) and at four time points after implementation of the intervention. The time points will include immediately post-intervention (T1) and at one-month post-intervention (T2), two months post-intervention (T3), and three months post-intervention (T4) for both the intervention and control groups. After three months of active intervention, the follow-up period will be passive. During the three-month follow-up, the intervention maintenance phase will be implemented. Additionally, the utilization of the Readiness to Behaviour Change Questionnaire is planned to assess the stage of behavioural change of students.

Exit interviews (approximately 50 interviews) will be conducted to elicit feedback and identify general challenges/barriers in executing the intervention from parents, teachers, and students as part of the research process

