### Statistical analysis

All analyses will be conducted on a modified intention-to-treat (ITT) population, comprising all randomized participants with a completed baseline and at least one completed valid post-baseline assessment.

The study will incorporate the use of generalized estimating equations (GEE) as the regression model to analyze the changes in study outcomes (social media use and its attributable child-family relationship, alcohol consumption, as well as sexual health issues) over the specified periods. The formal mathematical framework and specification of the GEE model equations are provided in S6 File. This comprehensive approach will provide more accurate and reliable insights into the effectiveness of the intervention across different socio-demographic variables, economic variables, and time intervals in the data.

The GEE model shall be adjusted for different socio-demographic and economic variables as well. GEE is applicable for both continuous and categorical study outcomes, and in the present study, the outcomes are both metric and categorical. For categorical outcomes, the GEE procedure can be executed with the maximum likelihood estimation (MLE) algorithm described

Additionally, a repeated measures analysis of ANOVA shall be used to study the effectiveness of the intervention across different periods of intervention. The statistical analysis shall be carried out using Stata version 17. The results will be considered statistically significant if the P-value is less than 0.05.

Further, the qualitative assessment of the exit interviews to elicit feedback and identify general challenges/barriers in executing the intervention will be analysed using thematic analysis and transcript interpretation by employing open-source MAXQDA software.

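### Cronbach's alpha is named as the measure of test-retest reliability, but as ordinarily computed it measures internal consistency at one sitting and does not show stability between sittings

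*Protocol article*

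**What the plan says.** The section on tools and materials lists five instruments: the Social Media Use Scale, the Family Relationship Scales, the Family Leisure Activity Profile, AUDIT and the Sexual Health Practice Tool. It describes three checks on them.

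- Content validity: "The questionnaire will undergo content validation in the North Indian context through expert review".
- Piloting: "Pre-testing on 10% of the sample (≈120 adolescents) will ensure clarity, with language corrections as needed".
- Reliability: "Test-retest reliability will be measured using Cronbach"'s alpha.

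The section states no second administration, retest interval, intraclass correlation, kappa or reliability threshold. It refers to supplementary files S2 and S3 for details of the tools; these are not shown.

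The Phase 3 section says the "tools will be administered at baseline (T0) and at four time points after implementation of the intervention". The Statistical analysis section uses GEE "to analyze the changes in study outcomes" over those periods.

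**The concern.** Test-retest reliability is the agreement between scores from the same people on two occasions. Alpha is normally a function of item variances and total-score variance at one occasion. A scale can have closely correlated items and still give a student a quite different score a fortnight later. The sentence therefore pairs a property with a statistic that does not estimate it.

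This is an error in what the article states, not a detail left to a fuller document. An analysis plan could correct the sentence only by contradicting it.

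Stability matters in this design because the same tools are repeated and changes are analysed. The tools are also being adapted to a local setting, with language corrections expected, so local reliability is a real question. The case is strongest for the Sexual Health Practice Tool, the only one of the five listed there without a source citation. The Results chain section counts validated tools among the study's inputs. If an alpha were entered under the test-retest heading, that claim would rest partly on a quantity that was not measured.

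**Working it through.** The article gives no reliability coefficient, so there is no figure of its own to reproduce. Two things can be checked.

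**Number of administrations.** T0 plus T1, T2, T3 and T4: 1 + 4 = 5.

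**Whether alpha tracks stability.** All inputs here are assumptions for illustration and none comes from the article: 10 items, trait SD 1, item error SD 1.2 (variance 1.44), and trait correlation ρ between two occasions. The figures below follow from closed formulas and agree with a simulation of 200,000 subjects.

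*Alpha at one occasion.*
- Item variance = 1 + 1.44 = 2.44, and the ten sum to 24.4.
- Variance of the total = 100 + 14.4 = 114.4.
- Alpha = (10/9) × (1 − 24.4/114.4) = 0.87.
- ρ does not enter the formula.

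*Retest ICC of the mean score, no shift between occasions.*
- Variance of the mean score = 1 + 1.44/10 = 1.144.
- Covariance between occasions = ρ.
- ICC = ρ/1.144.

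*Alpha with the two occasion totals treated as two items.*
- With equal variances, alpha = 2r/(1 + r), where r is the retest correlation. With no shift, r equals the ICC.
- This is the reliability of the average of two sittings, whereas the trial analyses single scores.

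| Trait correlation ρ | Alpha, one occasion | Retest ICC | Alpha on two occasion totals |
|---|---|---|---|
| 1.0 | 0.87 | 0.87 | 0.93 |
| 0.8 | 0.87 | 0.70 | 0.82 |
| 0.5 | 0.87 | 0.44 | 0.61 |
| 0.2 | 0.87 | 0.17 | 0.30 |
| 0 | 0.87 | 0 | 0 |

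*Adding a systematic shift of 0.5 trait SD at the second occasion.*
- The absolute-agreement ICC becomes ρ/(1.144 + 0.5²/2) = ρ/1.269.
- At ρ = 0.8 it falls from 0.70 to 0.8/1.269 = 0.63.
- Alpha on two occasion totals stays at 0.82, because a constant added to every second score changes neither the variances nor the covariance.

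So one-occasion alpha carries no information on stability. Two-occasion alpha carries some, but it exceeds the single-score value (0.82 against 0.70; 0.61 against 0.44) and does not register a shift.

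**The case against.** **Retest may imply a second sitting.** If so, the data would exist and only the statistic is misnamed. A reader might infer from the section that stability will go untested. The article does not support that: it neither describes a second sitting nor rules one out, and S2 and S3 are not shown. The objection stands as a limit on the consequence, but on either reading the named statistic is wrong.

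**Alpha can be computed across occasions.** This is true, so it would be too strong to say that alpha can never bear on retest reliability. The article does not say what its alpha is computed on. The two-occasion form is inflated for single scores and blind to a shift, so it does not rescue the sentence.

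**Alpha and yes/no questions.** A reader might add that alpha is meaningless for yes/no behaviours. That is not correct: for a set of dichotomous items it is defined (KR-20). It is undefined only for a single item. The item formats are in files not shown, so nothing here rests on them.

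**The tools are established.** The article calls them standardized and cites sources for four of the five. Whether those sources report stability cannot be checked here. In any case the article itself proposes to assess test-retest reliability, so it should do so with a suitable statistic.

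**The trial result is unaffected.** This largely stands. Schools are randomised, and both arms are assessed with the same tools at the same times. Random instability common to both arms mainly costs precision and power. A reader might infer bias in the between-arm contrast, but the article gives no ground for that.

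**Conclusion.** The stated method is wrong as written and should be corrected. Alpha, as ordinarily computed, measures internal consistency and would be misreported as stability. The conclusion rests on the definitions of the two properties, not on the illustrative figures. Those show that alpha can stay at 0.87 across the whole range of retest ICC from 0.87 to 0; they do not predict values for these instruments, for which the article gives no reliability data.

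The reach of the error is modest. It concerns validation of the instruments, and through any unreliable tool mainly precision and power. It does not alter the sample size calculation, the GEE analysis or the validity of the randomised comparison. Nothing in the article shows that any tool is in fact unstable.

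**What to change.** Replace the sentence with two.

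1. Internal consistency of the multi-item scales will be reported with Cronbach's alpha.
2. Test-retest reliability will be assessed from repeat scores on the same pre-test students at a stated interval. It will be reported as an absolute-agreement ICC with confidence interval for scale scores, and as kappa (weighted if ordinal) for categorical items.

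The length of the interval is for the investigators to choose and justify.

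**Cost.** If a second sitting is already planned within the pre-test of about 120 adolescents, only the wording and the computation change. If it is not, the cost also includes a repeat visit to those students. Recruitment began on 01/11/2025 according to the trial status section, so the pre-test may be over. If no second sitting was or will be done, relabel alpha as internal consistency and make no test-retest claim.

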#### Development and pre-testing of intervention.

The intervention will be developed and pre-tested using a mixed-methods approach, involving focus group discussions (FDGs), qualitative interviews, and pre-testing, with sample characteristics and sample size varying by stage.

According to Tynan and Drayton [14], 8–12 participants are needed for an FGD, with proportional selection of students, teachers, and parents. Following the Capability, Opportunity, Motivation-Behaviour (COM-B) model of behavioural change, the main aim of the FGD is to involve each stakeholder in assessing capability, opportunity, and motivation to change the behaviour of the school-going adolescents to address the issue of social media usage and its attributable adverse family-child relationship, alcohol usage, and sexual health issues. As per Boddy, a minimum of 6 FGDs in total will be conducted, with a minimum of 2 FGDs per study area, depending on the data saturation [15].

In total, 30 Qualitative interviews with the subject experts (mental health, social science & reproductive health) and the stakeholders of the intervention (students, parents & teachers) will be conducted [15]. Ten interviews per study area will be done with a proportionate number of stakeholders to identify the domains of the proposed social marketing intervention. For pretesting the intervention, a sample size of approximately 130 participants will be taken up (10% of the sample size for the intervention phase). The guides of the FGDs and qualitative interviews are attached in the S4 File.

#### Theoretical framework behind the intervention development.

This phase will follow an exploratory mixed-method study (qualitative formative research; quantitative content validity and pre-testing of the intervention) designed using the COM-B model of behavioural change. The COM-B system is a framework for understanding behaviour. In this ‘behaviour system,’ capability, opportunity, and motivation interact to generate behaviour that, in turn, influences these components [16]. Applying this to intervention design, the task is to identify the behavioural target and determine which components of the behaviour system need to be changed to achieve it.

